### Sample size

The power calculation concerns the comparison at T30 compared to T0 between the two groups (stepped care vs. care as usual). A recent meta-analysis on problem solving therapy for mental and physical health problems has documented an effect size of d = 0.54, compared to treatment as usual (compared to waiting list or no treatment, the effect size was d = 1.37; compared to attention placebo, the effect size was d = 0.54). Setting d = 0.5, alpha = 0.05 (two tail), beta = 0.80, the required sample size is 2 × 64 = 128 patients

A second power calculation was made concerning the difference in treatment effect over time (T0, T13, T30, and T42). Setting the within-subject correlation coefficient (rho) at 0.5, the required sample size following from this calculation is 2 × 42 = 84 patients.

The exclusion rate is estimated at 30% (primarily due to no informed consent). A detailed analysis of historical data has shown that the loss due to inclusion in other studies and mortality is 20%. The drop out rate is estimated at 20%. Consequently, 286 patients need to be invited for the study. On an annual basis, 80 autologous transplants are expected. Therefore, the inclusion period is 43 months.

## Discussion

This study design has several innovative characteristics. As to our knowledge, this is the first study in which the outcome of an intervention for psychological distress in patients with hematological malignancy treated with auto-SCT is evaluated in a randomized controlled protocol. Auto-SCT following high dose chemotherapy is a stressful treatment, leading to high levels of psychological distress [1]. Psychological follow up for patients treated with auto-SCT is in general not being systematically pursued; emotional support, advising on coping problems, and referring to other services usually occur on an ad hoc basis. To improve the quality of care and in order to reach more patients suffering from psychological distress following intensive hematological cancer treatment, it is essential to systematize and extend the follow up care.

The intervention in our study has been developed to improve patients' self-management and has been tailored to the needs of our specific patient group. Self-management is intended to help patients adjust to their condition and to improve their quality of life. The aims are to give patients control over their life and to obtain a proactive attitude in the patient [16]. Patients who are treated with auto-SCT for hematological malignancy, could therefore highly profit from improved self-management.

Furthermore, since psychological distress is a predictor of functional status in patients with hematological malignancy treated with auto-SCT [2-5], it is expected that the intervention will result in improvement of functional status if the intervention is successful in reducing psychological distress. The study is powered to evaluate the effect of the intervention on both psychological distress and functional status. Because (immuno-)chemotherapy and SCT have a strong impact on functional status, improved functional status as a consequence of reduced psychological distress would be a highly desirable outcome.

A third innovative characteristic of the present study is that the intervention aims at efficiency both in efforts and costs. This is reflected in the choice for a stepped care program, in which patients start with the least intensive treatment that is most likely to work, with more intensive and costly interventions reserved for those insufficiently helped by the initial self-help intervention. It is expected that most patients will be sufficiently helped by the Internet-based treatment, offered in step 1 [8]. Since there is minimal therapist contact, the therapist-time is being extremely reduced, the costs are low and there is no need for a waiting list [46]. Patients can systematically work on their self-management skills at any place and time they prefer.

Some patients will need more help than the Internet-based self-help program can offer them and will therefore enter step 2. A strength of this stage of the program is the multidisciplinary approach with a clear distribution of tasks and the nurse accomplishing a coordinating role. Multiple professional disciplines are brought together to treat the patients in the aftermath of disease. The collaborative team will evaluate the patients' need for treatment from various perspectives and subsequently develop the treatment plan. This collaboration of the various disciplines is coordinated by a nurse practitioner. Consequently, the professionals have the opportunity to deliver care efficacious and efficiently, and patients are assured of tailored care.

In the implementation of the stepped care program, nurses take up a central role. Especially during the phase of diagnostic evaluation and problem analysis, and during step 2, the nurse's contribution to treatment and care is essential. The nurse not only coordinates the collaborative team efforts, the development of the treatment plan, and the execution of it, but also assesses patients' case complexity and resulting care needs. Furthermore, the problem solving treatment sessions during step 2 are provided by a consultant psychiatric nurse.

The study also has some limitations that have to be taken into account. It could be that the most vulnerable patients will drop out of the experimental group because of difficulties completing the intervention program. This could reflect selective drop-out and lead to differences between the experimental and control group, because participants in the control group do not have to adhere to an intervention program, but only have to complete questionnaires. The data will be analyzed according to the intention to treat-principle. As a result, we will estimate the effects of allocating an intervention in practice, and not the effects in the subgroup of participants who adhere to the program. During the study, the drop out and (non-)compliance will be monitored. In a secondary analysis, patients completing treatment will be analyzed (per protocol analysis): this will allow us to estimate the effect of the intervention as such. Another limitation could be the length of the recruitment period. Given the long recruitment period, changes in medical treatment cannot be excluded. This may have impact on the intervention, although it is expected that patients in the intervention group and the control group will be affected in the same way.

If our trial shows a successful outcome, the intervention will be available for use in clinical practice. Results of this study will be available in 2014.

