From the existing literature we may conclude that psychological distress, specifically depression and anxiety, are predictors of functional status and other aspects of quality of life in patients treated with auto-SCT.

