#### Step 2: Contracting, individual face-to-face counseling, medication, or referral to other services

Patients meeting the criterion for psychological distress after completion of the Internet-based self-help program are offered further treatment. It is expected that approximately 50% of the patients will meet this criterion [8].

A collaborative team consisting of consultant psychiatrist, consultant psychiatric nurse, nurse practitioner (department of hematology), hematologist and patient is formed. The team evaluates the patient's need for treatment and develops the treatment plan. The nurse practitioner coordinates the team efforts, the development of the treatment plan and the execution of it. The team meets to develop tentative treatment options and to evaluate outcome of treatment.

Diagnostic evaluation is made by the consultant psychiatrist. The anxiety and depression modules of the Composite International Diagnostic Interview (CIDI) are administered for the classification of symptoms [25]. Additionally a standardized interview is held by the consultant psychiatric nurse, assessing the impact of distress on quality of life and the need for treatment. For this purpose, the Camberwell Assessment of Need (CAN) is used, measuring met and unmet needs on 22 domains of living [26]. The nurse practitioner and the consultant psychiatric nurse score case complexity and resulting care needs, using the Intermed [27,28]. Results of the diagnostic evaluation, standardized interview and scoring of case complexity are used by the collaborative team to analyze the existent problems, to evaluate the need for treatment and to develop tentative treatment options. The diagnostic evaluation, standardized interview and problem analysis are performed in a maximum of 4 weeks.

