### Statistical analysis

Primary outcomes are psychological distress as measured with the HADS and physical role function as measured with the EORTC-QLQ-C30. These primary outcomes reflect the central hypothesis of the study: stepped care is hypothesized to result in improvement in psychological distress, and thereby in improvement of functional status (see figure 1). Secondary outcome measures include: other measures of psychological distress; other aspects of quality of life; cognitions and coping.

Data are analyzed according to the intention to treat-principle. In a secondary analysis, a per protocol analysis will be performed. Baseline comparability of the experimental and control group is evaluated with descriptive statistics. The difference in outcome between stepped care and care as usual is evaluated by means of (mixed model) analysis of covariance. The randomization strata (hospital and diagnosis) will be included as covariates. In addition, a group*time-interaction term will be entered into the model to test for a difference in treatment effect over time. In analyzing a specific outcome variable, the baseline score of that variable is used as covariate.

If shown to be effective, we will explore whether patient characteristics (diagnosis, psychological distress, aspects of quality of life, cognition, coping, social support, and case complexity) moderate outcome of stepped care, using analyses of interaction between patient characteristics and treatment (stepped care vs. care as usual). Furthermore, we will explore which changes mediate outcome, by analyzing whether (a) change in psychological distress, (b) change in cognition, or (c) characteristics of the process of care mediate the outcome of stepped care, using the Baron and Kenny approach towards mediation and the Sobel test.

Both the analysis of moderating factors and the analysis of mediating factors is explorative in nature. This study is powered to answer the primary research question, i.e. the outcome of stepped care for psychological distress on functional status.

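### The secondary completers' analysis is said to give the effect of the programme itself, although the same section names selective drop-out from stepped care as a risk

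*Protocol article*

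**What the plan says.** The Statistical analysis section makes intention to treat the main analysis and adds: "In a secondary analysis, a per protocol analysis will be performed". The model is a (mixed model) analysis of covariance with hospital and diagnosis as covariates, and "In analyzing a specific outcome variable, the baseline score of that variable is used as covariate".

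The limitations part of the Discussion raises a risk: "It could be that the most vulnerable patients will drop out of the experimental group because of difficulties completing the intervention program". It continues: "This could reflect selective drop-out and lead to differences between the experimental and control group". The reason it gives is that "participants in the control group do not have to adhere to an intervention program, but only have to complete questionnaires". It then explains what intention to treat estimates and says that drop-out and compliance will be monitored. On the secondary analysis it states that "patients completing treatment will be analyzed (per protocol analysis): this will allow us to estimate the effect of the intervention as such". The warning about selection is not repeated for that analysis.

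Two other statements bear on the point. The Background concludes that "psychological distress, specifically depression and anxiety, are predictors of functional status and other aspects of quality of life", so vulnerability is taken to be prognostic for the outcomes. The description of step 2 says: "Patients meeting the criterion for psychological distress after completion of the Internet-based self-help program are offered further treatment". The amount of treatment there is to complete therefore depends on how a patient is doing after step 1.

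**The concern.** Randomisation makes the arms comparable as allocated. Restricting the analysis to patients who completed treatment conditions on something that happens after allocation. Here it bears mainly on one arm, because usual care contains no programme to complete. If those who stop have the poorer outlook, the remaining stepped-care patients look better than the controls even when the programme does nothing. The selection that the Discussion describes is thus the one to which a completers' analysis is most exposed, yet that analysis is presented as isolating the programme's own effect.

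What is at stake is interpretation. If the intention-to-treat result were null or borderline, the published wording would allow a completers' result to be reported as what the treatment achieves when taken. The Discussion says a successful outcome would make the intervention available for clinical practice.

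**Working it through.** **Benchmarks from the Sample size section.** No figure there is in dispute. With d = 0.5, two-sided alpha 0.05 and 64 per arm, the t-test has power 0.801, so 2 × 64 = 128 reproduces. The number to invite also reproduces: 128 / (0.7 × 0.8 × 0.8) = 285.7, or 286. The last 0.8 is the 20% drop-out rate. It is a trial-wide rate. The article gives no rate of programme non-completion, so 20% is borrowed as an assumption.

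**Check 1: vulnerable patients leave.** The true effect is set to zero. The worst 20% of the stepped-care arm on a vulnerability score V is removed and all controls are kept. The arms are then compared with and without adjustment for the T0 score. Inputs not in the article are the T0–outcome correlation ρ (0.3 to 0.7) and the correlation a of V with the outcome (0.3 or 0.7).

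Removing the top 20% of a standard normal V shifts its mean by φ(0.842)/0.8 = 0.280/0.8 = 0.35. The unadjusted bias is then 0.35 × corr(V, outcome). If V depends on the outcome with correlation a, the T0 mean shifts by 0.35aρ. Adjustment takes off about ρ times that, which leaves 0.35a(1 − ρ²). For example, 0.35 × 0.7 × (1 − 0.25) = 0.18. Simulation gives the following (SD units, in favour of stepped care):

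| What drives non-completion | ρ = 0.3 | ρ = 0.5 | ρ = 0.7 |
|---|---|---|---|
| Unrelated to prognosis | 0.00 | 0.00 | 0.00 |
| T0 score only, unadjusted | 0.10 | 0.18 | 0.25 |
| T0 score only, adjusted | 0.00 | 0.00 | 0.00 |
| V with a = 0.3, adjusted | 0.10 | 0.08 | 0.05 |
| V with a = 0.7, adjusted | 0.23 | 0.19 | 0.13 |

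With 10% to 30% removed, the adjusted bias in the outcome-related scenarios runs from 0.03 to 0.32 SD.

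**How strong is that selection?** Bias equals the non-completion rate times the gap between completers and non-completers that remains after adjustment. At 20%, a bias of 0.05 implies a gap of about 0.05/0.2 = 0.25 SD, and 0.23 implies about 1.15 SD, so the top of the range needs severe selection. A gap of 0.3 to 0.5 SD gives 0.06 to 0.10 SD. With 64 controls, 64 × 0.8 ≈ 51 completers and unit SD, the standard error is √(1/64 + 1/51) = 0.188. The nominal 5% test then rejects in 6.2% to 8.3% of null trials.

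**Check 2: selection through step 2.** This applies only if completing treatment includes step 2. About 50% are expected to qualify, on screening at T13. Treat them as the upper half of the T13 score, whose mean is 0.798 SD. Use the article's within-subject correlation of 0.5 between all visits, and let non-completion be random among those offered step 2. If 20% of the arm is excluded this way, the T13 mean of the rest shifts by 0.2 × 0.798/0.8 = 0.20. After T0 adjustment:

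- at T13 the bias is 0.20 × (1 − 0.25) = 0.15 SD;
- at T30 it is 0.20 × (0.5 − 0.25) = 0.05 SD.

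For exclusion of 10% to 30% of the arm, the ranges are 0.07 to 0.26 SD at T13 and 0.02 to 0.09 SD at T30. T0 adjustment does not remove this component, because the selection acts on a value measured after randomisation.

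**The case against.** The case for leaving the text alone has four parts.

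- **The text is conditional.** A reader might infer that the article predicts this drop-out, or that the estimate is certain to favour stepped care. Neither is supported. The Discussion says only that it could happen, and the direction follows only under that scenario.
- **Baseline adjustment is planned.** It can reduce the bias substantially, and in two of the scenarios above the adjusted bias is zero. A magnitude worked out without it overstates the problem. A reader might also assume 40% non-completion with a 0.5 SD gap and reach 0.4 × 0.5 = 0.20 SD and a null rejection rate near 17%, but nothing in the article supports 40%.
- **The per-protocol set is not fully defined.** Control-arm deviations, such as the psychological co-interventions on the process-of-care checklist, might also count. The detail may sit in the full protocol, so it cannot be said for certain that every control is retained.
- **The analysis is secondary.** Intention to treat is the main analysis and is correctly explained. No primary conclusion or sample size depends on the completers.

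All four stand, and they limit the size and importance of the point. They do not rescue the sentence. The unqualified claim needs either drop-out unrelated to prognosis or covariates that capture vulnerability fully. The article asserts neither, and its own warning points the other way.

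**Conclusion.** The claim attached to the completers' analysis is wrong as worded. The estimate is liable to bias, probably towards stepped care. On the assumptions in check 1 (20% non-completion, T0–outcome correlation 0.3 to 0.7, vulnerability–outcome correlation up to 0.7), the adjusted spurious benefit lies between 0 and about 0.2 SD, at most a little under half the design effect of 0.5 SD. The upper end requires strong selection that the T0 score does not capture. The primary intention-to-treat analysis is unaffected. This is a statement to correct before results are known, and it is not a flaw in the trial's main comparison.

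**What to change.** 1. In the Discussion, delete the clause claiming that the completers' analysis estimates the programme's own effect. There and in the Statistical analysis section, label that analysis supportive and subject to selection bias.

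2. If the effect of receiving the programme is of interest, estimate a complier-average causal effect with randomised arm as the instrument and the T0 score and strata as covariates. Take adherence from the process-of-care checklist, which already records the content of steps 1 and 2.

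3. Define adherence primarily as having started step 1, with completion as a sensitivity analysis. Under a completion definition, patients who used part of the programme count as non-adherent though they may have benefited, which strains the exclusion restriction. Under the starting definition, the restriction says that allocation has no effect on patients who never start. Check in the checklist that non-starters received no step 2 care.

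The cost is a few lines of text and code, with no new data and no change to design, sample size or primary analysis. The estimate is less precise: its standard error is about 1/0.8 = 1.25 times that of intention to treat at 80% adherence and 1/0.6 ≈ 1.7 times at 60%. It is not free of assumptions, and the exclusion restriction must be stated alongside it.

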## Ethical considerations

The study protocol has been approved by the Medical Ethical Committee of VU University Medical Center, Amsterdam, the Netherlands. All patients gave written informed consent.
